# Robotic radical antegrade modular pancreatosplenectomy (RAMPS) versus standard retrograde pancreatosplenectomy (SRPS): study protocol for a randomized controlled trial

**DOI:** 10.1186/s13063-020-04250-0

**Published:** 2020-04-03

**Keywords:** Robot-assisted, Distal pancreatectomy, Pancreatic surgery, Pancreatic cancer, RAMPS

## Abstract

**Background:**

Data from meta-analysis suggest that robotic radical antegrade modular pancreatosplenectomy (RAMPS) is a safe and effective procedure for treating adenocarcinoma in the body or tail of the pancreas, and is oncologically superior to standard retrograde pancreatosplenectomy (SRPS). RAMPS is an operation that actively expands the scope of resection, and achieves a higher R0 resection rate and lymph nodes acquisition through expanded resection. However, previous studies on RAMPS were conducted under open and laparoscopic surgery. Robotic surgery, on the other hand, plays a role in ergonomics and offers several advantages, including less fatigue, tremor filtering, 7° of wrist-like motion, motion scaling, and three-dimensional vision. At present, there is still a world-wide lack of clinical studies to observe the safety and clinical efficacy of robotic RAMPS. Hence, prospective randomized controlled trials (RCTs) comparing robotic RAMPS and SRPS are required. We begin an RCT to compare short-term surgical and oncological outcomes of robotic RAMPS and SRPS in patients undergoing distal pancreatectomy.

**Methods:**

This is a randomized, single-center clinical trial. All participants are adult patients with primary pancreatic cancer, who are undergoing RAMPS or SRPS. The primary endpoints are R0 rate (resection margins are classified by a margin to tumor distance ≥ 1 mm). The secondary endpoints are the number of harvested lymph nodes, perioperative complications and perioperative indicators (duration of surgery, blood loss, blood transfusion volume, costs).

**Discussion:**

We are undertaking a prospective RCT to evaluate the surgical and oncological outcomes of robotic RAMPS. This procedure may become a standard approach to robotic pancreatosplenectomy.

**Trial registration:**

Chinese Clinical Trial Registry: ChiCTR1900020833, Registered on 20 January 2019.

## Administrative information

Note: the numbers in curly brackets in this protocol refer to Standard protocol items: recommendation for interventional trials (SPIRIT) checklist item numbers. The order of the items has been modified to group similar items (see http://www.equator-network.org/reporting-guidelines/spirit-2013-statement-defining-standard-protocol-items-for-clinical-trials/).

## Introduction

### Background and rationale {6a}

Early diagnosis of pancreatic cancer is difficult, and the patient’s prognosis is extremely poor, with a 5-year survival rate of about 5% only [1]. Complete surgical resection is the only possible cure for pancreatic cancer, and microscopically margin-negative (R0) resection is the most important factor affecting postoperative survival in these patients [2–4]. Therefore, how to improve the rate of R0 resection in pancreatic surgery, and to delay and reduce local recurrence, has been a hotspot of pancreatic surgery research.

The positive rate of the peritoneal resection margin is high after SRPS, which is an important cause of tumor metastasis and recurrence. With progress in the concept of tumor treatment, surgical methods in the treatment of cancer in the pancreatic body and tail have improved. Strasberg et al. proposed RAMPS in 2003. Due to its theoretical rationality and good surgical outcome, it has attracted the attention of pancreatic surgeons. It is expected to become the standard surgical method for distal pancreatectomy [5].

The focus of RAMPS is on radical resection at the resection margin of the retroperitoneum. According to whether the tumor has invaded the posterior capsule of the pancreas, the anterior approach or the posterior approach have been used to improve the R0 resection rate of the resection margin of the retroperitoneum and the effect of radical resection of the tumor. RAMPS was reported a few years ago to significantly improve the R0 resection rate and 5-year survival rate compared with SRPS [5, 6]. However, reports in recent years have shown that despite the theoretic advantages of RAMPS over SRPS, high-level there is currently no evidence of a survival benefit with RAMPS [7, 8]. The potential advantage of RAMPS in terms of survival still needs to be proven.

The robotic surgical system plays an essential role in ergonomics and offers advantages to the surgeon, such as less fatigue, tremor filtering, 7° of wrist-like motion, motion scaling, and three-dimensional vision [9–12]. These characteristics mean that robots advantageous in delicate operations, in small spaces, in complex reconstruction, and in surgery involving blood vessels. Robotic surgery is likely to become mainstream in urological, gynecological, and other abdominal surgery in the future [13, 14].

## Objectives {7}

The aim of our study is to compare safety and the patient’s prognosis with robotic RAMPS and SRPS in the treatment of pancreatic body and tail cancer.

## Trial design {8}

This study is a single-center randomized controlled study in which patients will be assigned randomly into control and trial groups.

## Methods: participants, interventions and outcomes

### Study setting {9}

From August 2019 to 31 September 2022, patients will be selected from the Chinese People’s Liberation Army General Hospital (CPGH) for treatment. All patients must have been diagnosed with pancreatic body and tail cancer and meet the inclusion criteria. A total of 256 patients are scheduled to be included in the study. After confirmation of the eligibility criteria, including written informed consent, registration is made in the central registry in CPGH. Each patient will be randomly assigned a number in the central registry. Then, patients are randomized in a 1:1 allocation ratio either to arm A (RAMPS) or to arm B (SRPS), with a random block size (Fig. 1).

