### Sample size {14}

Determination of the marginal resection rate is the main endpoint of this study. Published reports describe an R0 resection rate of 50–74% in distal adenocarcinoma in studies with large sample sizes (*n* > 100 patients) [20, 21]. A systematic review of radical antegrade modular pancreatosplenectomy, which identified 13 observational studies involving 354 patients undergoing RAMPS, showed that the R0 resection rate was 88% [22]. According to these studies, we used a two-sided log-rank test, which requires about 23–123 patients in each group with 80% power at the 0.05 level of significance (NCSS and PASS 11 (NCSS Statistical Software, Kaysville, UT, USA)). Considering that there is a large gap in the estimated quantity of samples, we plan to collect 90 samples in each group. Considering a dropout rate of 10%, the total sample size required is 200 patients. After 50 samples have been collected in each group, we will make a mid-term comparison to determine whether there are significant differences between the groups. Based on the results, we decide whether or not to conduct further data collection.

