## Trial status

We are currently recruiting participants. The latest version is version 2.0 on 10 August 2019. The first participant was recruited on 6 September 2019, and the recruitment is expected to be completed in December 2020.

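### The protocol states two total sample sizes, 256 and 200; only 200 is derived, and the two differ by about 10 points of power at the conservative end of the planning range

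*Protocol article*

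**What the plan says.** Two sections of the protocol article give a total, and both are current text.

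- Study setting {9}: "A total of 256 patients are scheduled to be included in the study". The sentence carries no derivation.
- Sample size {14}: the section gives a requirement of 23 to 123 patients per group at 80% power, notes the wide gap, and settles between the two: "we plan to collect 90 samples in each group". It then states: "Considering a dropout rate of 10%, the total sample size required is 200 patients". It does not mention 256.

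The planning rates are in Sample size {14}. For the control side, "Published reports describe an R0 resection rate of 50–74% in distal adenocarcinoma"; for RAMPS, 88% from a systematic review.

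The calendar also appears in more than one form. Study setting {9} gives the selection window as "From August 2019 to 31 September 2022", and the consent section {26a} repeats that end date. Trial status says "the recruitment is expected to be completed in December 2020".

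**The concern.** The total sample size is a core protocol item, and here it has two values that differ by 56 patients (28% of 200). Because the article states both, this is a contradiction and not a detail left to a longer document.

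Two things are at stake. First, a reader cannot tell which power the trial was designed to have, and over part of the planning range the difference is material. Second, either stopping point could later be described as the planned one. Nothing in the text rules out settling on one after data have been seen.

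The dates do not resolve the matter, because neither end date is tied to either total.

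**Working it through.** **Inputs** (Sample size {14} unless noted): control R0 rate 50% to 74%; RAMPS R0 rate 88%; two-sided 0.05; 80% power; 90 evaluable per group; 10% dropout. Study setting {9}: total 256, allocation 1:1.

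**Step 1: reproduce the 23 to 123 per group.** Two-proportion test with pooled variance under the null and no continuity correction, where p̄ is the mean of the two rates:

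n = [1.960·√(2p̄(1−p̄)) + 0.842·√(p₁(1−p₁) + p₂(1−p₂))]² / (p₁−p₂)²

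- 50% vs 88%: (1.2819 + 0.5019)² / 0.38² = 22.04, so 23.
- 74% vs 88%: (1.0874 + 0.4594)² / 0.14² = 122.07, so 123.

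Both match. The section names a log-rank test, but its figures are those of a comparison of two proportions, so that test is used below.

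**Step 2: reproduce the 200.** 2 × 90 = 180 evaluable; 180 / 0.9 = 200. This matches.

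**Step 3: look for 256.**

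- Working back with the stated dropout: 256 × 0.9 = 230.4 evaluable, about 115 per arm. The article nowhere mentions 115.
- From the upper planning figure: 123 / 0.9 = 136.7, so 137 per group and 274 in total.
- With no loss: 256 / 2 = 128 per arm, which exceeds 123 but is not derived from it.

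No stated input produces 256.

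**Step 4: power under each total.**

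z = [|p₁−p₂|·√n − 1.960·√(2p̄(1−p̄))] / √(p₁(1−p₁) + p₂(1−p₂)); power = Φ(z)

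At 74% vs 88% the constants are 0.14, 1.0874 and 0.5459:

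- n = 90 (200 less 10%): (1.3282 − 1.0874)/0.5459 = 0.441, power 67.0%.
- n = 115 (256 less 10%): (1.5013 − 1.0874)/0.5459 = 0.758, power 77.6%.
- n = 100 (200, no loss): (1.4000 − 1.0874)/0.5459 = 0.573, power 71.7%.
- n = 128 (256, no loss): (1.5839 − 1.0874)/0.5459 = 0.910, power 81.8%.

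The same formula across the control range, with RAMPS at 88% (62% and 70% are illustrative points inside the stated range):

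| Control R0 rate | 90 per arm | 115 per arm |
|---|---|---|
| 50% | >99.9% | >99.9% |
| 62% | 98.5% | 99.7% |
| 70% | 85% | 92% |
| 74% | 67% | 78% |

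**Step 5: dates.** September has 30 days, so 31 September 2022 is not a date. December 2020 is about 21 months before the end of September 2022.

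**The case against.** The conflict between 256 and 200 is hard to dispute. Reading 256 as a screening number does not help: the sentence speaks of inclusion, and no screening-failure rate is given. The strong objections are to what might be built on the conflict.

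- **Error rate.** A reader might infer that two permissible totals amount to an extra look and so inflate the type I error. The documents do not support that as a fact. Sample size {14} and Interim analyses {21b} describe one interim comparison, at 50 per group or 100 in total. No section provides for an analysis at 200 followed by continuation to 256. What stands is only that the text does not exclude it. Any error-rate problem of the 100-patient comparison exists under either total and is a separate matter.
- **Interim timing.** A reader might also infer that the interim is left undefined. Its trigger is an absolute count on which both sections agree, and no boundary in the article depends on a fraction of the total.
- **Power.** The 10-point gap belongs to the 74% end. At a 50% control rate the choice of total makes no practical difference. This stands, and the gap should be quoted only with its condition.
- **Which figure is the error.** It is tempting to treat 256 as the slip because only 200 is derived. But 200 falls short of the stated 80% power at 74% vs 88%, while 128 per arm exceeds the stated upper requirement of 123. That does not derive 256, but it is reason not to presume that 200 is right.
- **Dates.** The Trial status date is a forecast that falls inside the longer window, so it need not contradict it. The impossible date affects no calculation. This stands, and the dates are a minor point.

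**Conclusion.** The point holds as an internal inconsistency in the sample size. The arithmetic behind 200 is correct; the fault is that a second, underived total of 256 stands beside it and nothing in the article reconciles them.

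The size of the effect depends on the control rate. At 74% vs 88% the choice moves power from about 67% to about 78% if 10% are lost, or from about 72% to about 82% if none are. Only 256 with no loss reaches the stated 80% at that end. At 50% both totals exceed 99.9%.

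These figures assume a two-sided two-proportion test at 0.05 without continuity correction, an 88% RAMPS rate, equal arms and loss of either 10% or none. They make no allowance for the interim comparison.

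The documents show no intention to choose between the totals once results are known. The finding is that the final size is open on paper, which should be corrected before the 100-patient comparison.

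**What to change.** 1. State one total in both Study setting {9} and Sample size {14}, with its derivation: assumed rates, evaluable number per group and dropout. The sponsor must say which total was intended.
2. Beside it, give the power across the 50–74% control range. If 200 is kept, say that power is about 67% at 74% vs 88% with 90 evaluable per arm, not 80%. If 256 is kept, add the missing derivation and say that power there is about 78% after 10% loss.
3. State that the final analysis is done once, when that number is reached.
4. As a minor correction, replace 31 September 2022 with a real date in Study setting {9} and the consent section {26a}, and align it with Trial status, for example by saying that December 2020 is a forecast within the permitted window if that is what is meant.

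The cost is a wording amendment. The stated sizes differ by 56 patients, so whether more are needed than now expected depends on which total the sponsor intended.

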**Fig. 1 Fig1:**
[figure not shown]
Consolidated standards of reporting trials (CONSORT) flow diagram. RAMPS, radical antegrade modular pancreatosplenectomy; SRPS, standard retrograde pancreatosplenectomy

### Eligibility criteria {10}

#### Inclusion criteria

The inclusion criteria are:
Informed consent signed by the patient or his or her legal agent;Compliance with the study plan and follow-up procedure;Men or women ages 18–70 years;No surgical contraindications, able to tolerate radical surgery, Eastern Cooperative Oncology Group (ECOG) behavioral status score 0–1, life expectancy ≥ 12 weeks, American Society of Anestheologists (ASA) score ≤ 2;Tumor diagnosed as resectable on preoperative pathological examination or clinical judgment;Tumor meets the indications required for resection of pancreatic somatococcygeal carcinoma by robot.

#### Exclusion criteria

The exclusion criteria are:
Malignant tumors elsewhere in the body within the last 5 years;Brain, lung, bone, or abdominal lymph node metastases;Severe cardiopulmonary function, or infection affecting liver or renal function;Pregnancy or lactation.

#### Participating surgeons

Differences in the surgical experience of surgeons may lead to differences in the incidence of complications. By analyzing the perioperative data from the first 100 cases of robotic pancreaticoduodenectomy performed by a single surgeon in our center, we found that the surgeon's learning cure was completed after performing 40 such operations. The duration of surgery, intraoperative blood loss and incidence of complications in the patients were significantly decreased [15]. In this research, our surgical team consists of three surgeons and each of these clinicians meet the participation requirements and have received adequate training prior to participating in the study. Patients will be randomly assigned to each surgeon’s group.

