### Outcomes {12}

#### Endpoints

The primary efficacy endpoint of the trial will be the rates of resection margins. In the case of malignant pancreatic disease, resection margins are classified by a margin to tumor distance ≥ 1 mm (R0), a margin to tumor distance < 1 mm (R1) or a macroscopically positive margin (R2) [18]. The secondary endpoints are (1) the number of harvested lymph nodes; (2) retrieval postoperative complications including pancreatic fistula, intra-abdominal abscess, and anastomotic leakage, according to the Clavien-Dindo classification (Table 1): complications classified as higher than grade II are regarded as clinically significant [19]; and (3) perioperative indicators; such as duration of the operation, blood loss, blood transfusion volume, rate of transition to open surgery, postoperative hospitalization days, and hospital costs.

**Table 1 Tab1:** Complication grades according to the Clavien-Dindo classication scheme

Grade	Definition
V	Death of patient
IV	Life-threatening complication. Requiring intensive care unit management
IVa	Single organ dysfunction
IVb	Multi-organ dysfunction
III	Requiring surgical, endoscopic, or radiological intervention
IIIa	Intervention not under general anesthesia
IIIb	Intervention under general anesthesia
II	Requiring pharmacological treatment with drugs other than those allowed for grade I complications
I	Any deviation from the normal postoperative course without the need for pharmacological treatment or surgical, endoscopic, and radiological intervention

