### Concealment mechanism {16b}

Patients are randomized in a 1:1 allocation ratio either to arm A (RAMPS) or to arm B (SRPS), with a random block size (Fig. 1).

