## Assignment of interventions: blinding

### Who will be blinded {17a}

The experiment was a single-blind trial. Patients will not know their grouping. Surgeons perform operations according to their group.

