## Statistical methods

### Statistical methods for primary and secondary outcomes {20a}

Statistical analysts do not participate in clinical observation. They will be blinded to allocation and responsible for statistical analysis of research data and timely delivery of statistical reports to the research director. All analyses will be performed and reported in accordance with the Consolidated standards of reporting trials (CONSORT) statement and the ICH E9 “Statistical Principles in Clinical Trials”. Primary and secondary outcomes will be cross-checked against data. The measurement data are expressed as mean plus/minus standard deviation. The normality test and homogeneity test of variance will be performed first. The independent sample *t* test will be used to compare normally distributed continuous variables, and the values will be represented as the mean with standard deviation. Continuous non-normally distributed variables will be compared using the Mann-Whitney *U* test, and the values will be expressed as the median of the quartile spacing. The categorical variables are compared using the chi-square test or the Fisher’s exact test, and values will be expressed as proportions with corresponding risk ratios and 95% confidence intervals. *P* < 0.05 indicates statistical significance. Statistical analysis will be performed using SPSS 20.0 software.

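### Patients are randomly assigned among three surgeons, but the R0 and secondary-outcome tests ignore surgeon: no bias, but a little precision is given up needlessly

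*Protocol article*

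**What the plan says.** All references are to the protocol article.

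- **Participating surgeons.** "Differences in the surgical experience of surgeons may lead to differences in the incidence of complications". The section then says "our surgical team consists of three surgeons" and "Patients will be randomly assigned to each surgeon", that is, to that surgeon's group. How this assignment is made, and how it is linked to the arm, is not described.
- **Concealment mechanism {16b}** (and Study setting {9}). "Patients are randomized in a 1:1 allocation ratio either to arm A (RAMPS) or to arm B (SRPS), with a random block size". No stratification factor is named.
- **Outcomes {12}.** "The primary efficacy endpoint of the trial will be the rates of resection margins". R0 is treated as yes or no by a 1 mm margin. Lymph nodes, operating time and blood loss are among the secondary endpoints.
- **Statistical methods {20a}.** "The categorical variables are compared using the chi-square test" or Fisher's exact test. Continuous outcomes get a t test or a Mann-Whitney test. None of these has a surgeon term.
- **Methods for additional analyses {20b}.** Surgeon is mentioned once, as a subgroup analysis to be done in the future.
- **Who will be blinded {17a}.** "Surgeons perform operations according to their group". The sentence does not say whether the group meant is the patient's arm or the surgeon's own group.

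**The concern.** The plan names surgeon as a factor that changes outcomes and assigns patients by it, then leaves it out of the stated tests. That is a choice the text makes, not a detail left to another document. When a known factor explains part of the outcome, a comparison within its levels is usually sharper than a crude one. If allocation is also balanced by that factor, the crude test's standard error is too large.

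Precision matters here because the planned 90 per group is below the 123 that the article's own range gives at its less favourable end.

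**Working it through.** **Inputs from the article.** "Published reports describe an R0 resection rate of 50–74% in distal adenocarcinoma" for the comparator; 88% for RAMPS; two-sided 0.05; 90 evaluable per group; three surgeons.

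**Assumptions.** Surgeon-specific R0 rates, equal surgeon shares, and a common odds ratio across surgeons. The article gives no R0 rate by surgeon, so a range is shown.

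**1. The plan's own figure.** Two proportions, pooled variance under the null, no continuity correction:

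n = [1.96·√(2p̄(1−p̄)) + 0.8416·√(p₀(1−p₀)+p₁(1−p₁))]² / (p₁−p₀)²

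- 50% vs 88%: (1.2820 + 0.5019)² / 0.1444 = 22.04, so 23.
- 74% vs 88%: (1.0874 + 0.4594)² / 0.0196 = 122.1, so 123.

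Both ends of the stated 23–123 reproduce. With 90/0.9 = 100 per arm, so does the total of 200.

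**2. Power of the crude test at 90 per arm, 74% vs 88%.**

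- Null SE = √(2·0.81·0.19/90) = 0.0585.
- Alternative SE = √((0.74·0.26 + 0.88·0.12)/90) = 0.0575.
- Power = Φ((0.14 − 1.96·0.0585)/0.0575) = Φ(0.44) = 67.0%.

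**3. How large chance imbalance between surgeons is.** If surgeon and arm are assigned independently, the expected bias is zero. The chance shift in the R0 difference (under no treatment effect) has SD √(2·Var(p_k)/90), where p_k are the surgeons' rates.

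- 64/74/84%: Var = (10² + 0² + 10²)/3 = 66.7, so SD = √(133.3/90) = 1.2 points.
- 54/74/94%: Var = (20² + 0² + 20²)/3 = 266.7, so SD = √(533.3/90) = 2.4 points.

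This is not noise on top of the crude SE of about 5.8 points. It is already inside the binomial variance that the chi-square test uses. It is the part that adjustment can remove.

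**4. Gain from adjustment.** Simulated trials, 40,000 per setting, 90 per arm, RAMPS mean 88%. Crude chi-square against a surgeon-stratified Cochran-Mantel-Haenszel (CMH) test without continuity correction:

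| Comparator R0 by surgeon | Unstratified: crude → CMH | Balanced within surgeon: crude → CMH |
|---|---|---|
| 74/74/74% | 67.3 → 66.9 | 67.4 → 67.5 |
| 68/74/80% | 67.5 → 67.8 | 67.6 → 68.1 |
| 62/75/85% | 67.9 → 68.9 | 67.7 → 69.2 |
| 55/77/90% | 67.6 → 71.1 | 68.2 → 71.7 |

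The Monte Carlo SE of one entry is √(0.67·0.33/40,000) = 0.24 points. A separate run of 100,000 trials with balanced allocation gave 67.8 → 69.0 at 64/74/84% and 68.1 → 72.1 at 54/74/94%. Nearly all the gain comes from adjusting and little from stratifying the allocation. At 50% vs 88% crude power already exceeds 99.9%, so nothing is gained there.

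**5. Type I error of the crude test.**

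- Unstratified allocation: 4.8% to 5.0% across all spreads.
- Balanced within surgeon: the true variance is the crude one times 1 − Var(p_k)/(p̄(1−p̄)).
  - 64/74/84%: 1 − 0.00667/0.1924 = 0.965, so 2·(1−Φ(1.96/√0.965)) = 4.6% (simulated 4.5%).
  - 54/74/94%: 1 − 0.02667/0.1924 = 0.861, which gives 3.5% (simulated 3.5%).

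**The case against.** **The crude test is valid and the gain is small.** This stands. With both assignments random, surgeon and arm are independent by design. A reader might infer that they are partly confounded, but the documents do not support that: chance imbalance has zero expected bias and the 5% level already covers it.

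**The surgeon spreads are invented.** This also stands, and it limits the size claimed. The article links experience to complications, operating time and blood loss in another operation, not to R0. It also says all three surgeons met the participation requirements and were trained. A 40-point spread in R0 within such a team is an extreme case.

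**Lack of stratification is inferred from silence in a condensed article.** Agreed. The point therefore does not rest on it: the tests are stated without a surgeon term, and adjustment helps under either allocation.

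**A tempting stronger reading.** The sentence in the blinding section could be taken to mean that each surgeon works in one arm only. Surgeon and arm effects could then not be separated, and the test would not hold its level. The documents do not support this reading. The sentence follows one about patients not knowing their grouping and reads most naturally as surgeons carrying out the operation of the patient's arm. Patients are assigned to surgeons at random with no stated link to arm. A subgroup analysis by surgeon would have nothing to compare if each surgeon served one arm. What remains is a wording ambiguity.

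**Conclusion.** The point holds as a small efficiency improvement to a stated method. It is not a finding of bias or invalidity. Leaving surgeon out costs about 0 to 1 power point for small to moderate surgeon differences (up to 1.5 if allocation is balanced within surgeon) and about 4 for very large ones, starting from about 67%. If allocation is balanced within surgeon, the crude test is slightly conservative. These sizes rest on assumed surgeon rates, equal surgeon shares, a common odds ratio, and every surgeon operating in both arms. No size was computed for the secondary outcomes, although operating time, blood loss and complications are where the article itself reports an effect of experience. Adjustment does not close the gap between 90 and 123 per group.

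**What to change.** - **Statistical methods {20a}.** Make the primary R0 test a CMH test stratified by surgeon, with the Mantel-Haenszel risk ratio and its 95% confidence interval. Specify it without continuity correction: in the two-proportion calculation above, the correction raises 123 per group to 136, which would outweigh the gain. Include surgeon as a factor in the models for lymph nodes, operating time and blood loss. Keep the crude tests as sensitivity analyses.
- **Participating surgeons and Who will be blinded {17a}.** Reword the two together so that it is clear how surgeons' groups relate to the arms. The adjusted comparison requires each surgeon to operate in both.
- **Allocation.** Blocking within surgeon is optional. Trial status says the first participant was recruited on 6 September 2019, so it could apply only to patients not yet randomised.

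**Cost.** A few sentences. Surgeon must be recorded anyway for the intended subgroup analysis, and no extra patients or data are needed. The change should be made before outcomes are compared by arm, including at the interim analysis at 100 patients.
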